### Power Analysis

Group sample sizes of 106 in the Positive Peer group and 106 in the control group achieve 90% power to detect a difference between group proportions of 0.20. This is the minimum sample size required in each group to detect the desired difference in proportions. The proportion in group 1 (the treatment group) is assumed to be 0.60 under the null hypothesis and 0.80 under the alternative hypothesis. The proportion in group 2 (the control group) is 0.60. The test statistic used is the 2-sided *Z* test with pooled variance. The significance level of the test was set at .05. Several assumptions regarding baseline viral suppression were tested based on the literature. The current sample size is based on 63% viral suppression at baseline and a planned 80% in the intervention group. If baseline viral suppression is lower, a smaller sample size would be needed to demonstrate a 20% improvement in viral suppression. Based on this estimation, we aim to recruit and randomize 250 eligible individuals to the study from 6 clinic sites over 24 months, allowing for potential loss to follow-up. It is important to note that patients without documentation of a clinic visit during the assessment period are designated as out of care and will be assumed to be HIV virally unsuppressed. Available data on other outcomes and covariates, however, will be handled using mixed-effects models, which employ maximum likelihood estimation and assume missing-at-random patterns to support valid inferences.

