### Study Rationale and Objectives

We expect the PPA to support engagement in HIV care by normalizing and rewarding care visits, promoting health literacy, reducing stigma, and enhancing inclusion, thereby allowing users to help others with similar challenges. Our goal is to increase HIV viral suppression rates by at least 15% by offering practical and peer support through a smartphone app. Specific aims addressed by the protocol described in this manuscript are (1) comparing the effectiveness of HIV care supported by the PPA with usual care for improving retention in HIV care and viral suppression among high-priority adolescents and young adults with HIV; (2) identifying factors that predict user engagement with primary PPA components and associated effects on retention in care, viral suppression, and HIV-related perceived stigma; and (3) evaluating PoPIT implementation across sites and over time. Figure 1 illustrates the conceptual model of the PoPIT study’s influence and outcomes. This paper describes the protocol used to achieve these aims in a randomized clinical trial with a concurrent qualitative evaluation focused on user experience.

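### The Power Analysis gives two incompatible bases for one sample size: 106 per arm has about 90% power at 60% vs 80%, but only about 79% at 63% vs 80% if 63% is the comparator rate

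*Protocol article*

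**What the plan says.** All the inputs are in one paragraph, under Power Analysis in the protocol article.

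- Sample size and power: "Group sample sizes of 106 in the Positive Peer group and 106 in the control group achieve 90% power", for a difference of 0.20.
- Treatment proportion: it "is assumed to be 0.60 under the null hypothesis and 0.80 under the alternative hypothesis".
- Control proportion: "The proportion in group 2 (the control group) is 0.60".
- Test and level: "The test statistic used is the 2-sided *Z* test with pooled variance", and "The significance level of the test was set at .05".

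After noting that several baseline suppression rates from the literature were tried, the paragraph states: "The current sample size is based on 63% viral suppression at baseline and a planned 80% in the intervention group".

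It then sets a target of 250 randomized participants to allow for loss to follow-up, and says that patients with no documented visit in the assessment period will be counted as unsuppressed. No separate sample size or power is given for 63% vs 80%.

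**The concern.** Two pairs of rates are each presented as what the sample size rests on. The first is 0.60 vs 0.80, a difference of 20 points. The second is 63% vs 80%, a difference of 17 points. One sample size with one stated power cannot rest on both, because three points matter at this size of effect. The required number changes with the inverse square of the difference, and (0.20/0.17)² is about 1.38.

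This is the only power calculation in the article. Suppression at 6 months is one of the two clinical outcomes of the randomized comparison, and the one that the calculation is built on. Anyone interpreting a non-significant result will look back to the stated 90%. If the planning scenario was really 63% vs 80%, the chance of missing that effect with 106 per arm is about 21%, roughly twice the 10% the reader is told.

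**Working it through.** **Inputs.** All are from the Power Analysis section, with 1:1 allocation from Study Design: n = 106 per arm; two-sided alpha .05 (z = 1.96); 90% power (z = 1.2816); pooled-variance Z test; rate pairs 0.60/0.80 and 0.63/0.80. The 250 to be randomized make 125 per arm.

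**Formulas.** Let p̄ be the mean of the two proportions, d their difference, A = √[2p̄(1−p̄)] and B = √[p₀(1−p₀) + p₁(1−p₁)].

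- n per arm = (1.96·A + 1.2816·B)² / d²
- Power = Φ[(d·√n − 1.96·A) / B]

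**Step 1: reproduce the stated figure, 0.60 vs 0.80.** p̄ = 0.70, A = √0.42 = 0.6481, B = √0.40 = 0.6325, d = 0.20.

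- n = (1.2702 + 0.8106)² / 0.04 = 4.330 / 0.04 = 108.2, so 109 per arm.
- Power at 106 = Φ[(0.20 × 10.296 − 1.2702) / 0.6325] = Φ(1.247) = 89.4%.
- With unpooled variance, n = (1.96 + 1.2816)² × 0.40 / 0.04 = 105.1, so exactly 106 per arm, with 90.2% power.

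The stated 106 and 90% therefore reproduce for this pair. The gap between 106 and 109 is only the variance convention.

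**Step 2: the other pair, 0.63 vs 0.80.** p̄ = 0.715, A = √0.40755 = 0.6384, B = √0.3931 = 0.6270, d = 0.17.

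- n = (1.2513 + 0.8035)² / 0.0289 = 4.222 / 0.0289 = 146.1, so 147 per arm (294 in total). Unpooled variance gives 143 per arm (286 in total).
- Power at 106 = Φ[(0.17 × 10.296 − 1.2513) / 0.6270] = Φ(0.796) = 78.7%.
- Power at 125 = Φ[(0.17 × 11.180 − 1.2513) / 0.6270] = Φ(1.036) = 85.0%.

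**Step 3: does the method matter?** At 63% vs 80% with 106 per arm, the unpooled form gives 79.7%, the arcsine form 79.1% and exact binomial enumeration of the pooled test 79.1%. Even a one-sided test at .05 reaches only 86.8%.

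**Step 4: could the 80% be the slip?** A true 20-point difference from 63% is 63% vs 83%. The pooled formula then needs 102 per arm and gives 91.2% at 106.

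| Rates | Difference | n per arm for 90% | Power at 106 per arm | Power at 125 per arm |
|---|---|---|---|---|
| 60% vs 80% | 20 points | 109 | 89.4% | 93.7% |
| 63% vs 80% | 17 points | 147 | 78.7% | 85.0% |
| 63% vs 83% | 20 points | 102 | 91.2% | 95.0% |

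(Two-sided pooled Z, alpha .05.)

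**The case against.** **The 63% is not called a control rate.** This is correct. The paragraph names one control proportion, 0.60, and labels the 63% as suppression at baseline. A reader might infer that the article states two control rates, but it does not. If 63% is only a pre-enrolment rate and 60% is the rate expected in the control arm at 6 months, the 106 figure stands and the fault lies in the sentence about the basis. The article does not say this, however. It sets the 63% directly against the intervention arm's 80% and calls that pair the basis of the current size. Reading it as the comparator is fair, but it remains a reading.

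**The 90% claim is not false as written.** This is also correct. The claim is attached to a 0.20 difference with 0.60 vs 0.80, and it reproduces there. It fails only when carried over to 63% vs 80%. Nor can it be said that 106 fits 60% vs 80% alone, since 63% vs 83% fits about as well.

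**The planned 250 is the more relevant number.** This largely stands. Patients without a visit are counted as unsuppressed, and Planned Statistical Analysis defines suppression as a proportion of enrolled patients, so many losses stay in the denominator. At 63% vs 80% the shortfall is then about 5 points of power rather than 11. It does not vanish, and the extra 38 participants were added for loss to follow-up, not for a smaller effect.

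**The 15% goal.** Study Rationale and Objectives says "Our goal is to increase HIV viral suppression rates by at least 15" per cent. A reader might infer a third, conflicting target for which the trial is underpowered. The article does not support that. The sentence is an aspiration and not a sample-size input, it does not say whether the figure is absolute or relative, and planned gains of 17 or 20 points both satisfy it. Power for a 15% gain need not be reported.

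**Conclusion.** The point holds as an unreconciled contradiction about the basis of the sample size. For 60% vs 80% the stated 90% is right to rounding. For 63% vs 80% it is not reached: power is about 79% with 212 analysed and about 85% with all 250, against about 147 per arm needed for 90%. The size of the shortfall depends on two assumptions. One is that 63% acts as the comparator rate. The other, for the 85%, is that the 63% and 80% apply to all randomized participants, with those lacking a visit already counted as unsuppressed. If the first assumption is wrong, the sample size is sound and one sentence misdescribes its basis. Either way the paragraph needs correcting.

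**What to change.** Keep the sample size. State one control-arm suppression rate at 6 months and one absolute target difference, and report the matching power. The sponsor knows which of these applies:

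- **63% vs 80% is the basis:** replace the 0.60 figures and state about 79% power with 212 and about 85% with 250.
- **60% vs 80% is the basis:** keep about 90% and correct the 63% sentence. If 63% is only a pre-enrolment rate, say so.
- **A 20-point gain from 63% was meant:** correct the 80% to 83% and the control rate to 63%, with about 91% power at 106 per arm.

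The cost is the rewording of one paragraph and, under the first option, a less favourable stated power. No participants are added, and neither the design nor the analysis changes.

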## Methods

### Study Design

Specific aims and corresponding hypotheses will be evaluated in a randomized controlled trial that compares HIV outcomes in patient groups randomized to either immediate or delayed access to the PPA. The delayed-start design is intended to ensure that both randomized study conditions receive identical study procedures, follow-up, reminders, incentives, and assessments during the first 6 months of participation. The only difference is the timing of app access. Any improvement observed in the delayed-start group during this period can therefore be attributed primarily to nonspecific effects of trial participation. The primary randomized comparison at 6 months thus estimates the incremental benefit of the app beyond these common trial effects. A greater improvement in outcomes in the immediate-start group at this point would provide evidence of a specific impact of the app.

Prospective questionnaires will be administered at baseline and at 3, 6, 9, and 12 months to provide evidence for model-specific hypotheses and the mediating effects of covariates and demographics. We have included an opportunity for patients who decline full study participation to grant permission to the PoPIT team to abstract their HIV outcomes from medical records on the same schedule as full study participants. This observation-only arm includes only the baseline questionnaire and medical record review of study outcomes. The inclusion of an observational cohort in the randomized controlled trial design strengthens external validity by enabling comparison of trial participants with the broader clinic population. By comparing outcomes from both randomized controlled trial arms with those of the observational cohort, we will gain additional insight into how trial participation may influence outcomes and how the intervention might be further adapted for a more diverse clinical population.

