### Reminders and Notifications

The PoPIT study uses an automated alert and reminder system for follow-up questionnaire invitations. Reminders are keyed to each participant’s study enrollment date and study arm through the REDCap database system. Based on participant preferences, questionnaire invitations and reminders are sent via SMS text message or email. If contact information changes during the study, this is either reported directly by a participant to site staff or becomes apparent when a routine questionnaire invitation or reminder message is returned as undeliverable. Regular verification of contact information is emphasized to site staff as a critical component of project implementation and is continuously monitored. First, this routine outreach is an integral component of the PPA, functioning as an extension tool for clinical staff to promote engagement in care and support strategies outside the clinical encounter. Outside the trial environment, users receive notifications about updates and new features. Second, PPA includes a customizable notification system for the medication tracker, community forum, chat function, and event scheduling. Users can enable or disable these reminders and schedule the dates and times at which they are sent. Users may also opt in or out of notifications related to forum and chat activity. A third type of notification used in PPA is EMAs.

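### The control-arm suppression rate in the power calculation is justified as a baseline value; no 6-month control rate is given, and the 90% power holds for the planned 80% only if that rate is about 60%

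*Protocol article*

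**What the plan says.** The Power Analysis section of the protocol article sets up a two-group comparison: "Group sample sizes of 106 in the Positive Peer group and 106 in the control group achieve 90% power", for a between-group difference of 0.20, with a two-sided pooled Z test at .05. The treatment proportion "is assumed to be 0.60 under the null hypothesis and 0.80 under the alternative hypothesis", and "The proportion in group 2 (the control group) is 0.60".

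The same paragraph then explains where the rates come from. It says that several assumptions about suppression at baseline were examined from the literature, and: "The current sample size is based on 63% viral suppression at baseline and a planned 80% in the intervention group". It adds that a lower baseline rate would reduce the number needed to show a 20% improvement. The recruitment target is 250. Patients with no documented visit in the assessment period count as unsuppressed.

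Study Design defines the contrast differently. Both randomized arms receive the same trial procedures for 6 months, any improvement in the delayed-start arm is attributed mainly to nonspecific trial effects, and "The primary randomized comparison at 6 months thus estimates the incremental benefit of the app beyond these common trial effects".

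**The concern.** The quantity that drives power here is the suppression rate in the delayed-start arm at month 6. The only justification offered is a rate at entry. Sizing on 63% at baseline against 80% in the app arm is before-to-after reasoning, and it equals the between-arm difference only if the control arm does not move in 6 months. The design does not assume that: it uses a concurrent control so that any movement can be subtracted.

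Entry requires a recent diagnosis, being out of care, or not being suppressed (Sample Population). A rate measured at entry in such patients says little about their rate after 6 months of clinic care with trial follow-up, in either direction.

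At stake is how a null result is read. If the control rate at month 6 is some points above 60% and the app arm reaches its planned 80%, the trial has materially less than 90% power, and a non-significant result would be taken as stronger evidence against the app than it is.

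**Working it through.** **Inputs (Power Analysis).** Control p1 = 0.60; app arm p2 = 0.80; n = 106 per arm; two-sided alpha .05; pooled Z test. The target of 250 gives 250/2 = 125 per arm if everyone is analysed. This is a reasonable upper case, because a patient with no visit is scored as unsuppressed and not dropped.

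**Formula.** Power = Φ[(d − 1.96·s0)/s1], with d = p2 − p1, s0 = √(2·p̄(1 − p̄)/n), p̄ = (p1 + p2)/2, and s1 = √((p1(1 − p1) + p2(1 − p2))/n).

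**Step 1: reproduce the stated figure.** For 0.60 versus 0.80 and n = 106: s0 = √(2 × 0.70 × 0.30/106) = 0.0629; s1 = √((0.24 + 0.16)/106) = 0.0614; (0.20 − 1.96 × 0.0629)/0.0614 = 1.247; power = 89.4%. The pooled sample-size formula gives 109 per arm for 90%; the unpooled one gives 105.07, that is 106. The stated figure reproduces.

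**Step 2: the document's own 63%.** For 0.63 versus 0.80 and n = 106: s0 = 0.0620; s1 = 0.0609; (0.17 − 1.96 × 0.0620)/0.0609 = 0.796; power = 78.7%. For 90% power, 147 per arm would be needed.

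**Step 3: vary the 6-month control rate.** The document gives no value above 63%, so 65% and 70% are assumptions. Three ways of carrying the effect forward are shown, because the answer depends on which one is meant.

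| Control rate at 6 months | App arm fixed at 80%: power at 106 / 125 | 20-point difference kept: power at 106 / 125 | Odds ratio kept: power at 106 / 125 |
|---|---|---|---|
| 60% | 89% / 94% | 89% / 94% | 89% / 94% |
| 63% | 79% / 85% | 91% / 95% | 88% / 92% |
| 65% | 69% / 76% | 92.5% / 96% | 86% / 91% |
| 70% | 39% / 45% | 96% / 98% | 82% / 87% |

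The odds ratio implied by 60% versus 80% is (0.80/0.20)/(0.60/0.40) = 2.67. It puts the app arm at 82.0%, 83.2% and 86.2% for control rates of 63%, 65% and 70%.

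**Step 4: which reading does the paragraph itself use?** It says that a lower baseline needs fewer patients. With 80% held fixed that is true: 50% versus 80% needs 52 per arm, against 109 for 60% versus 80%. With a 20-point difference held fixed it is false: 50% versus 70% needs 124. The remark therefore works only with 80% fixed, and under that reading a higher control rate must cost power.

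**Step 5: detectable difference.** With 125 per arm and 90% power it is 18.7 points at a 60% control rate, 17.9 at 65% and 16.7 at 70%.

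**The case against.** The strongest reply is that the calculation is already a concurrent two-group test: the paragraph opens by saying that the sample sizes "achieve 90% power to detect a difference between group proportions of 0.20", it names a control proportion, and its power reproduces. That stands. The fault lies in the justification of 0.60, not in the test or the arithmetic.

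A second reply is that effects common to both arms would lift both, so the app arm need not stay at 80%. This also stands as a possibility. The table shows power kept at a constant difference and modestly reduced at a constant odds ratio. It does not remove the point, because 80% is the only app-arm target in the document and the remark about a lower baseline depends on holding it fixed.

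A third is that the direction is uncertain. The entry criteria may put true baseline suppression below 60%, and scoring no visit as unsuppressed lowers the month-6 rate in both arms, so 60% could prove right. This is fair, and it is a further reason to state and defend the month-6 rate.

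Two stronger readings are tempting and not supported. A reader might infer that the control arm is expected to improve; Study Design speaks only conditionally of any improvement observed, and no section predicts or quantifies one. A reader might also infer from Reminders and Notifications ("this routine outreach is an integral component of the PPA, functioning as an extension tool for clinical staff to promote engagement in care") that controls receive an active part of the app. The trial reminders described there and under Quantitative Data Collection and Measures are for questionnaires, the incentives pay for questionnaires, interviews and momentary assessments, and what the outreach sentence refers back to is unclear. The first aim's wording ("comparing the effectiveness of HIV care supported by the PPA with usual care") is looser than the contrast actually made, but Study Design already describes that contrast correctly, so this is secondary.

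**Conclusion.** The point holds in a limited form. The control proportion is justified by a baseline rate (60% in the calculation, 63% in the text), and no 6-month control rate is given for a comparison made at 6 months. The 90% power is right for 0.60 versus 0.80. With the app arm at the planned 80%, it applies only if the control arm is near 60% at month 6: at 106 (125) per arm, power is 79% (85%) at 63%, 69% (76%) at 65% and 39% (45%) at 70%.

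The losses at 65% and 70% rest on two assumptions: that the control arm reaches those rates, which the document does not predict, and that the app arm stays at 80%. If the 20-point difference persists, there is no loss. The mismatch between 60% and 63% is a separate inconsistency; resolving it would still leave a baseline value standing in for a follow-up rate.

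**What to change.** In Power Analysis:

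- State the assumed 6-month suppression rate in the control arm as it is run (usual care plus the trial procedures, with no visit counted as unsuppressed), and give its basis.
- Remove the wording that sizes the trial on improvement from a baseline rate, and reconcile 60% with 63%.
- Keep the sample size. Report power for control rates of about 60% to 70%, once with the app arm fixed at 80% and once with the difference fixed at 20 points. Alternatively, report the detectable difference at 90% power with 125 per arm: about 19, 18 and 17 points at control rates of 60%, 65% and 70%.

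The cost is a rewritten paragraph and a small table, with no extra patients and no change to design or analysis. The stated power will look less favourable under the fixed-80% reading.

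### The power paragraph names two different pairs of rates as the basis of one sample size; under 63% vs 80%, 106 per arm gives about 79% power, not 90%

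*Protocol article*

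**What the plan says.** Everything at issue is in one paragraph of the protocol article, Methods, Power Analysis.

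The paragraph opens with a full specification: "Group sample sizes of 106 in the Positive Peer group and 106 in the control group achieve 90% power to detect a difference" of 0.20 between the group proportions. The treatment proportion "is assumed to be 0.60 under the null hypothesis and 0.80 under the alternative hypothesis", and "The proportion in group 2 (the control group) is 0.60". The test is given as well: "The test statistic used is the 2-sided *Z* test with pooled variance", at the .05 level.

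A few lines later, after noting that several assumptions about baseline suppression were examined, the paragraph says: "The current sample size is based on 63% viral suppression at baseline and a planned 80% in the intervention group". It gives no second sample size for this second pair. The next sentence speaks again of a 20% improvement. The one after it builds the recruitment target of 250 randomised participants on this estimation, with an allowance for loss to follow-up.

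**The concern.** The two statements give different inputs for the same number. The first pair is 0.60 and 0.80, a difference of 0.20. The second is 0.63 and 0.80, a difference of 0.17. The second is not offered as a sensitivity case: it is said to be what the current sample size is based on. A reader cannot tell which pair supports 106 per arm, 90% power and the target of 250.

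The choice matters. Required sample size grows roughly with the inverse square of the difference, so a loss of 3 points from 20 is costly. If 63% is the operative assumption, the 90% claim is wrong for the basis the document itself names. Should the trial end without a significant difference, readers will rely on that claim when judging what the result excludes.

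**Working it through.** **Inputs, all from the protocol article.** From Power Analysis: 106 per arm; stated power 90%; two-sided Z test with pooled variance; alpha .05; first pair 0.60 and 0.80; second pair 0.63 and 0.80; 250 to be randomised. From Study Design: 1:1 allocation, hence 250/2 = 125 per arm. No loss rate is stated.

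**Formulas.** With d = p1 − p2 and p̄ = (p1 + p2)/2:

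- Power = Φ( [d − 1.96·√(2p̄(1−p̄)/n)] / √([p1(1−p1) + p2(1−p2)]/n) )
- n per arm for 90% power, pooled = [1.96·√(2p̄(1−p̄)) + 1.2816·√(p1(1−p1) + p2(1−p2))]² / d²
- n per arm for 90% power, unpooled = (1.96 + 1.2816)²·[p1(1−p1) + p2(1−p2)] / d²

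**Step 1: the plan's own figure, 0.60 vs 0.80.** Here p̄ = 0.70, 2p̄(1−p̄) = 0.42, and the sum of the two variances is 0.16 + 0.24 = 0.40.

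- Power at n = 106: [0.20 − 1.96·√(0.42/106)] / √(0.40/106) = (0.2000 − 0.1234)/0.0614 = 1.247, so Φ = 89.4%.
- The unpooled version gives 90.2%, and exact binomial enumeration of the pooled Z test gives 89.6%.
- n for 90% power: 109 pooled, 106 unpooled.

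So 106 and 90% do come from 0.60 vs 0.80. The shortfall of 0.6 points under the pooled formula is immaterial and is not part of this point.

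**Step 2: the pair named as the basis, 0.63 vs 0.80.** Here p̄ = 0.715, 2p̄(1−p̄) = 0.40755, and the sum of the variances is 0.2331 + 0.16 = 0.3931.

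- Power at n = 106: [0.17 − 1.96·√(0.40755/106)] / √(0.3931/106) = (0.1700 − 0.1215)/0.0609 = 0.796, so Φ = 78.7%.
- Power at n = 125: (0.1700 − 0.1119)/0.0561 = 1.036, so Φ = 85.0%.
- n for 90% power, pooled: (1.2512 + 0.8035)²/0.0289 = 146.1, so 147 per arm.
- n for 90% power, unpooled: 142.9, so 143 per arm.

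**Step 3: does another convention rescue 90% at 106 per arm?**

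| 0.63 vs 0.80, 106 per arm | Power |
|---|---|
| Pooled Z, two-sided | 78.7% |
| Unpooled Z, two-sided | 79.7% |
| Arcsine, two-sided | 79.1% |
| Exact enumeration of the pooled Z test | 79.1% |
| Pooled Z, one-sided (not the plan's test) | 86.8% |

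None does. With a continuity correction the requirement rises to 158 per arm.

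**Step 4: compare with enrolment.** 90% power at 0.63 vs 0.80 needs 2 × 143 = 286 to 2 × 147 = 294 evaluable participants, against 250 randomised.

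**Step 5: could 63% go with a 20-point gain?** That would be 63% vs 83%. It needs 102 per arm, and 106 per arm gives 91.2% power. But the text states 80%, not 83%.

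**The case against.** The strongest reply has three parts.

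First, the operative calculation can be identified. The opening sentences specify it fully, the arithmetic confirms it, and the later sentence may be left over from one of the other scenarios examined. That is probably so, but it explains the contradiction without removing it. The sentence says the current size is based on 63% and 80%, so it is wrong as it stands.

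Second, 63% is described as a baseline rate, while the control rate is stated separately as 0.60. The 79% figure does depend on reading 63% as the control rate, and it should be given with that condition. The sentence sets 63% against the planned 80% as its comparator, which supports the reading. If 63% never entered the calculation, the sentence is false for that reason instead. Whether a baseline rate may stand in for the control rate at 6 months is a separate question, not raised here.

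Third, 106 per arm may be too pessimistic. Participants with no documented clinic visit in the assessment period are counted as unsuppressed, so many of those lost would stay in the denominator, and the analysed number could be close to 125 per arm. This stands in part: the relevant power then lies between about 79% and 85%. It does not reach 90% at either end. Counting such participants as unsuppressed could also shift the rates themselves, which the document gives no means to quantify.

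**Conclusion.** The paragraph contradicts itself, and the stated 90% power holds for only one of its two input pairs. For 0.60 vs 0.80 the claim is right within rounding. For 0.63 vs 0.80, power is about 79% with 106 evaluable per arm, so the type II error is about 21% rather than 10%. With all 250 analysed, power is 85.0% and the type II error about 15%. These figures assume that 63% is the control-arm rate and use the two-sided .05 pooled Z test and 1:1 allocation that the protocol states. The endpoint, the test, the alpha level and the conduct of the trial are unaffected; what is wrong is the stated justification of its size.

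**What to change.** State one pair of rates and the power that follows from it. Two wordings would do:

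- **Keep the calculation.** Change the 63% sentence so that it says the sample size uses 60% in the control group and 80% in the intervention group. The 106 per arm and 90% then stand.
- **Keep 63% vs 80%.** Restate power as about 79% with 106 evaluable per arm and about 85% with 125 per arm. Change the 0.20 difference to 0.17, and drop the statement that 106 is the minimum needed for the desired difference at 90% power. Bring the following sentence about a 20% improvement into line.

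If 63% was only one of the scenarios examined, it can be reported as a sensitivity case with its own power figure.

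The cost is a few sentences in the protocol, and in the analysis plan if it repeats them. The correction itself requires no change in enrolment. Under the second wording the published power becomes less favourable.

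Recruitment is planned to run until November 27, 2026, so the record can be put right before results are known.

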### Sample Population

The study is designed to evaluate the effects of the PPA intervention among the age group most likely to be newly diagnosed with HIV in the United States: adolescents and young adults. This cohort is challenged by a propensity for greater risk behavior, lower health literacy and management skills, and typically less favorable social determinants of health. Potential participants are identified as patients at 1 of 5 HIV care organizations serving as study sites, located across 6 priority jurisdictions where HIV transmission occurs most frequently. Patients are screened to determine whether they meet all necessary inclusion criteria for study participation (Textbox 1).

Positive Peers Intervention Trial eligibility criteria.Inclusion criteriaHIV-positive status, either newly diagnosed within the last 12 months, out of care (without an office visit in the last 12 months), or not virally suppressed (viral load >200 copies/mL within the last 12 months).Adolescents and young adults aged 13-34 receiving care at one of the study sites.Identification with a sexual, gender, racial, or ethnic minority.Participant’s capacity to provide informed consent (aged >16 years) or assent to participate (aged <16 years).Ownership of a smartphone/tablet (either iOS or Android) capable of supporting the Positive Peers mobile app.Ability to read English.Exclusion criteriaPrevious use of the Positive Peers mobile app.Adults older than age 34 at the time of enrollment.Not a patient at one of the participating clinical sites.

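### The power section says a lower baseline suppression rate would need a smaller sample; for the plan's own 20-point difference the required sample is larger

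*Protocol article*

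**What the plan says.** The Power Analysis section of the protocol article states the calculation as follows.

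- Size and power: "Group sample sizes of 106 in the Positive Peer group and 106 in the control group" are said to "achieve 90% power to detect a difference between group proportions of 0.20".
- Treatment-arm rate: it "is assumed to be 0.60 under the null hypothesis and 0.80 under the alternative hypothesis".
- Control-arm rate: "The proportion in group 2 (the control group) is 0.60".
- Test: "The test statistic used is the 2-sided" Z test with pooled variance. "The significance level of the test was set at .05".

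The section then reports that several baseline suppression assumptions were tried, and describes the sample size as resting on 63% at baseline and 80% with the intervention. It adds: "If baseline viral suppression is lower, a smaller sample size would be needed to demonstrate a 20% improvement in viral suppression". The recruitment target is 250 randomized, to allow for loss to follow-up. Patients with no documented clinic visit in the assessment period are counted as unsuppressed.

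The eligibility box under Sample Population requires HIV-positive patients to be "either newly diagnosed within the last 12 months, out of care (without an office visit in the last 12 months), or not virally suppressed".

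**The concern.** The sentence tells the reader what happens if the baseline assumption is too high, and its answer is that the trial would then need fewer patients. For a fixed difference between two proportions, the required number depends on the sum of the two binomial variances. That sum grows as the pair of rates moves towards being centred on 50%. With a 20-point gap the pair is centred on 50% when the control rate is 40%. A fall from 60% towards 40% therefore raises the required number.

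A lower rate is also a scenario worth getting right here. Entry is through recent diagnosis, absence from care or non-suppression, and patients without a visit count as failures. A reader who sees a low suppression rate during the trial could conclude from this sentence that power is better than planned, when for a 20-point gain it is somewhat worse.

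**Working it through.** **Inputs, all from Power Analysis.** Two-sided alpha 0.05 (z = 1.960), power 90% (z = 1.2816), pooled-variance Z test, control rate p0 = 0.60, intervention rate p1 = 0.80, 106 per arm, 250 randomized (125 per arm at 1:1).

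**Formulas.** With m = (p0 + p1)/2:

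- n per arm = [1.960·√(2m(1−m)) + 1.2816·√(p0(1−p0) + p1(1−p1))]² / (p1 − p0)²
- power = Φ{ [(p1 − p0)·√n − 1.960·√(2m(1−m))] / √(p0(1−p0) + p1(1−p1)) }

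**Reproducing the plan's figure.** For 0.60 versus 0.80, m = 0.70, 2m(1−m) = 0.42, and the sum of variances is 0.24 + 0.16 = 0.40. Then n = (1.960 × 0.6481 + 1.2816 × 0.6325)² / 0.04 = 108.2, so 109 per arm. The version with unpooled variance gives 10.507 × 0.40 / 0.04 = 105.1, so 106, which is the stated number. Power at 106 with the pooled test is 89.4%. The 106 is reproduced closely enough and is not in dispute.

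**Lowering the control rate with the difference held at 0.20.** The true control rate is an assumption, shown over a range.

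| Control rate | Sum of variances | n per arm for 90% power | Power at 106 per arm | Power at 125 per arm |
|---|---|---|---|---|
| 60% | 0.400 | 109 | 89.4% | 93.7% |
| 55% | 0.435 | 118 | 86.8% | 91.7% |
| 50% | 0.460 | 124 | 84.9% | 90.2% |
| 45% | 0.475 | 128 | 83.8% | 89.3% |
| 40% | 0.480 | 130 | 83.4% | 89.0% |
| 30% | 0.460 | 124 | 84.9% | 90.2% |
| 20% | 0.400 | 109 | 89.4% | 93.7% |
| 15% | 0.355 | 97 | 92.5% | 95.9% |

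The curve is symmetric about a control rate of 40%. The requirement is above the 60% value everywhere between 60% and 20%, equals it at 20%, and drops below it only under 20%. Starting from 63% gives the same direction: 63% versus 83% needs 102 per arm, against 130 at 40%.

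**Lowering the control rate with the intervention rate held at 80%.** The required n per arm is 147 at 63%, 109 at 60%, 72 at 55%, 52 at 50% and 30 at 40%. Here the number does fall, but the gains are 17, 20, 25, 30 and 40 points.

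**The two stated control rates.** 63% versus 80% is a difference of 0.17. It needs 147 per arm. Power is 78.7% at 106 per arm and 85.0% at 125.

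**The case against.** The strongest defence reads the sentence in its place. The sentence before it sets 63% against a planned 80%. If the 80% target is held and the baseline drops to 60%, the gap becomes exactly 20 points and the requirement falls from 147 to 109 per arm. On that reading the sentence correctly describes one step. This stands for the step from 63% to 60% and no further: at 55% the gain with a fixed 80% target is already 25 points, which is not the improvement the sentence names. The defence also depends on the 63% figure, which conflicts with the 60% used in the calculation.

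The defence is also right that the consequence is small. The plan randomizes 125 per arm, and because patients without a visit are counted as unsuppressed, many losses may stay in the analysis. With all 125 per arm analysed, power for a 20-point gain never falls below 89%.

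Three stronger readings are tempting, and the article does not support them.

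- **A relative 20%.** A reader might take the improvement as relative, in which case 50% to 60% would need 519 per arm. The section defines the effect as a difference in proportions of 0.20, so this is not the plan's question.
- **A low control rate as the expected case.** The eligibility criteria describe status at entry. The number needed depends on control-arm suppression at 6 months, after newly diagnosed and returning patients have had usual care. The article gives no figure for that rate.
- **No other sensitivity check.** The section says several baseline assumptions were tried, and the full protocol or analysis plan may report them. Neither is shown.

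**Conclusion.** The concern holds in a limited form. For the plan's own effect, an absolute difference of 0.20, the sentence gives the wrong direction for control rates between 60% and 20%. At 106 per arm the cost is up to 6 points of power: 89% at a 60% control rate, 83% at 40%. At 125 per arm power falls from 94% to 89%.

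These figures rest on the stated two-sided pooled Z test and a control rate that has to be assumed. They do not show that the trial is seriously underpowered or that 106 was miscalculated.

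The unreconciled 60% and 63% control rates matter about as much. Taken literally, 63% versus 80% leaves about 79% power at 106 per arm.

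Severity is moderate: a false statement in the sample-size justification, cheap to correct, with a small effect on power.

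**What to change.** In Power Analysis:

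1. Delete the sentence, or replace it with a statement that for a fixed 20-point difference the required number rises as the control rate falls from 60% towards 40%.
2. Say that the 20% is an absolute difference in percentage points.
3. State that for control rates of 40% to 50%, power for a 20-point gain is about 83% to 85% at 106 per arm and 89% to 90% at 125 per arm.
4. Reconcile the two control rates. If 63% versus 80% is the real assumption, say that this is 17 points, needs 147 per arm, and has about 79% power at 106 and 85% at 125. If 60% versus 80% is the assumption, remove the 63% statement or explain what it refers to.

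The cost is a few sentences and a slightly less favourable stated power. Enrolment, design and analysis need not change.
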